## Abstract

**Background**: Elderly people are affected by processes leading to decline in various aspects of daily living that impair their quality of life. Regarding neurological aspects, executive functions have been shown to be valuable for daily life and to slow decline during aging. Most intervention studies intended to improve cognitive functions during aging specifically address long-term destructive processes and countermeasures. However, to an increasing degree, studies also investigate the acute benefits that prove to be useful for daily life, such as physical exercise or video games in the form of exercise video gaming (“exergaming”). Because little is known about the change in cognitive ability following acute intervention of a combination of physical exercise and video gaming, especially for older people, this work is designed as an attempt to address this matter.

**Methods**: This study is a randomized crossover controlled trial to test the response to an acute bout of high-intensity physical exercise followed by a short session with a brain training (Brain Age) video game in physically active and cognitively healthy older adults (60–70 years). The response is measured using Stroop task performance (cognitive task for executive function) and related brain activity assessed with functional magnetic resonance imaging (fMRI). The control conditions are low-intensity physical exercise and Tetris for video gaming.

**Discussion**: This study is intended to provide insight into the alteration of executive function and its related brain activity from an acute intervention with a combination of physical exercise and video gaming in older people. The protocol might not be implementable in daily life to improve cognitive abilities. However, the results can support future studies that investigate cognition and the combination of physical exercise and video gaming. Moreover, it can provide real-life implications.

**Trial registration**: This trial was registered in The University Hospital Medical Information Network Clinical Trials Registry (UMIN000033054). Registered 19 July 2018, https://upload.umin.ac.jp/cgi-open-bin/ctr/ctr_view.cgi?recptno=R000037687.

## Background

Elderly people experience processes leading to decline in various aspects of daily living that impair their quality of life. Regarding neurological aspects, the executive functions, which include aspects such as working memory, inhibition, and cognitive flexibility (Diamond, 2013), have been shown to be valuable for daily life. Nevertheless, they decline during aging. Executive functions are important for processes such as planning and at a later time for executing objectives successfully, and for using prospective memory (Hering et al., 2014; McDaniel et al., 2014). Prospective memory has been shown to be associated with and to decline with processes such as working memory, inhibition, and shifting, which are executive functions (Hering et al., 2014). Various positive attempts have been undertaken for improving or at least preserving executive functions in several ways, e.g., nutrition, physical training, and cognitive training (Kramer et al., 2003; Kueider et al., 2012; Johnson, 2013). Eventually, it might not be just one, but rather a combination of these options that will help to improve quality of life (Phillips, 2017). Most reported intervention studies that improve cognitive functions have emphasized long-term application of at least 1 month or longer (Brehmer et al., 2012; Cheng et al., 2012). However, lately, studies also increasingly investigate the acute benefits that prove to be useful for daily life (Roig et al., 2013), such as those related to physical exercise (Tomporowski, 2003) or video games in the form of exercise video gaming (“exergaming”; Monteiro-Junior et al., 2017). This work was undertaken to address this matter because little is known about the change in cognitive ability and its related brain activity using fMRI following an acute intervention of a combination of physical exercise and video gaming, especially for older people.

### Physical Exercise

Acute bouts of physical exercise can be implemented in daily life as part of a morning routine. They are already performed in Asian countries such as Japan (Yamashita et al., 2001). When examining physical exercise as an acute intervention, its benefits for cognitive abilities can be discussed intensively, such as whether moderate-intensity or high-intensity exercise is superior. For more details please see the “Discussion” section. Meta-analyses conducted by Chang et al. (2012) and Ludyga et al. (2016) reveal that, with regard to executive functions, older adults (Johnson et al., 2016) especially benefit from acute intervention with physical exercise and demonstrate that the benefit is independent of the current fitness level. For that reason, untrained people can receive cognitive benefits just as trained people do. This study uses a high-intensity physical exercise intervention and applies cognitive tests after a delay of approximately 20 min. This delay will be used to apply the video game intervention. The question of whether greater cognitive improvement is found after high-intensity physical exercise compared to low intensity should be answered. Moreover, we must ascertain whether this benefit can be enhanced by combining the intervention with brain training video gaming.

### Video Gaming

Video games elicit cognitive benefits (Granic et al., 2014), even in older adults (Zelinski and Reyes, 2009; Toril et al., 2014; Stanmore et al., 2017). Older adults are increasingly interested in playing video games (Zelinski and Reyes, 2009). They might have some potential for improving health-related issues, also in a clinical and rehabilitation framework (Primack et al., 2012; García-Betances et al., 2015). Nevertheless, the outcomes of video gaming for older adults are quite controversial. A meta-analysis from Toril et al. (2014) shows that cognitive functions of older adults benefit from video gaming in general, but it also revealed that executive functions do not reach significant levels. Other studies have revealed that the executive functions can be enhanced in older adults (Basak et al., 2008; Green et al., 2012; Strobach et al., 2012; Anguera et al., 2013). For a more detailed consideration please refer to the “Discussion” section. The usage of video games for acute interventions is on the rise, but many aspects remain to be answered (Guzmán and López-García, 2016; Monteiro-Junior et al., 2017). A salient question is: which game should be used for this purpose? First, it should have a beneficial effect on executive functions. Second, it should be conducted as an acute session to fit in the 20-min pause after the physical exercise. Third, the video game should be interesting also for older adults. One video game that fulfills all these requirements is Brain Age (Nintendo Co. Limited, Kyoto, Japan), also known as [name] Training. It is a popular brain training series based on the scientific work of [name] developed for handheld consoles from Nintendo (Kawashima et al., 2005; Uchida and Kawashima, 2008). It is meant to improve cognitive functions merely by playing a few minutes a day. Results demonstrated that common tasks among others such as simple arithmetic calculations and fast reading are beneficial for the executive functions (McDougall and House, 2012; Nouchi et al., 2012). Because Brain Age has only been conducted in a long-term setting with older adults (Nouchi et al., 2012), it is now to be examined whether it can also enhance the executive function in older adults in an acute intervention and whether there are additive effects if applied immediately after physical exercise.

### Combination of Physical Exercise and Video Gaming

For some people, physical exercise alone might be too boring to perform regularly. Combining it with video gaming in for example, “exergaming” (combination of physical exercise and video gaming), might improve compliance (Mat Rosly et al., 2017) and create engaging exercising programs for rehabilitation (e.g., decrease risk for falls; Hasselmann et al., 2015). Video games are meant to be fun; they excel at inducing the so-called flow (Sherry, 2004; Chen, 2007), which is a state of an individual when the challenge presented by a certain task matches the skill of this individual (Belchior et al., 2012). This state itself has beneficial effects on cognitive function (Shafer and Carbonara, 2015), which can be superior to usual cognitive training at least to some degree (Anguera and Gazzaley, 2015; Shute et al., 2015). Because exergaming is fun and emerging (Maillot et al., 2012; Verheijden Klompstra et al., 2014; Eggenberger et al., 2015; Lyons, 2015), it has a more positive influence on compliance than those of other rehabilitation methods. It “may be an effective way to promote physical and cognitive improvements among older adults” (Maillot et al., 2012).

One issue of studies investigating exergaming is that it is difficult to measure the extent of physical activity during such activities: do they really “exercise” or are they too passive? The approach such as that used in this study protocol to use physical exercise and video gaming separately but sequentially gives the opportunity to combine different conditions mutually. Consequently, it is distinguishable between the attribution of the different conditions to the improvement of the cognitive ability or the change in brain activity when measured in fMRI.

Because there might be different mechanisms affecting how physical exercise and video gaming respectively improve cognitive abilities (for additional details, see “Discussion” section), apart from the behavioral improvement at the cognitive test, differences in brain activity following different interventions will be recorded using functional magnetic resonance imaging (fMRI).

## Brain Activity in Elderly People During Physical Exercise and Video Gaming

This section specifically addresses what is known about brain activity in older adults with respect to cognitive tasks in general and after an acute intervention with physical exercise or with video gaming.

### Neural Correlates for Stroop Task in Elderly People

For older adults, neural substrates of the Stroop task using fMRI have usually been bilateral activations, especially of the anterior cingulate cortex (ACC) and lateral and medial frontal areas such as the left lateral prefrontal cortex (LPFC; Langenecker et al., 2004; Huang et al., 2012); the left inferior gyrus is particularly important for performance on the Stroop task (Langenecker et al., 2004). Prakash et al. (2009) compared differences in activation patterns of younger and older adults as the difficulty increases in Stroop task. Increasing difficulty is usually coupled with an increase of activation by younger adults. In older adults, while showing already increased activation intensity at baseline, this increase is absent. This absence is especially true for the dorsolateral prefrontal cortex (DLPFC). The conclusion is that older adults are not flexible anymore and are not able to adapt to higher difficulties, which underscores the necessity for recruiting additional brain areas to compensate for the decline in performance.

### Brain Activity of Elderly People After Physical Exercise

Considering how the brain activity of older adults changes after physical exercise, few reports describe studies that have investigated its acute effects either without neuroimaging (Kamijo et al., 2009) or in younger adults with neuroimaging such as fMRI (Li et al., 2014) and functional near-infrared spectroscopy (fNIRS; Yanagisawa et al., 2010; Tempest et al., 2017). Hyodo et al. (2012) have conducted the only study investigating the acute effects of moderate-intensity physical exercise on Stroop task performance in older adults using fNIRS as neuroimaging. No report of the relevant literature describes an investigation of acute effects of physical exercise conducted with fMRI (Voss et al., 2011), except for a report by Li et al. (2014), who investigated the working memory of younger female adults using N-back task.

Hyodo et al. (2012) described activation of the bilateral DLPFC, ventrolateral prefrontal cortex (VLPFC), and frontopolar area (FPA): the same brain areas as those reported by Langenecker et al. (2004) for older adults at rest. Especially, the right frontopolar area (R-FPA) is the neural substrate of improved cognitive performance after an acute bout of moderate exercise in older adults. Results suggest that during aging, R-FPA compensated for deterioration of the left dorsolateral prefrontal cortex (L-DLPFC), which is usually activated after physical exercise in younger adults (Hyodo et al., 2012). R-FPA activation has also been observed during Stroop interference in fMRI studies (Milham et al., 2001; Zysset et al., 2001). The Stroop reaction time correlates inversely with the activation of R-FPA.

### Brain Activity of Elderly People After Video Gaming

Alteration of brain activity through cognitive training or video games is not well understood. The activation patterns for executive function tasks after cognitive training differ (Di et al., 2014). Some reports have described increased activation in the prefrontal cortex after intervention (Olesen et al., 2004; Westerberg and Klingberg, 2007), but others have described decreased activation (Babiloni et al., 2009; Del Percio et al., 2009; Wartenburger et al., 2009; Gobel et al., 2011). Behavioral improvement of Stroop task performance after video gaming, especially for Brain Age, has been shown in younger adults after a long-term intervention (Nouchi et al., 2013), but no study has examined the conduct of an acute session of Brain Age in older adults as well as its neuroimaging.

Taking what can be expected about the acute intervention regarding the brain activity together, it can be concluded that an acute session of high-intensity physical exercise in older adults possibly engenders increases in activation of DLPFC, VLPFC, and FPA, but R-FPA especially correlates with better performance at the Stroop task. For video gaming, it can only be assumed that an acute session can affect brain activation in a way that either optimizes processes or exploits resources leading respectively to a decrease or increase in brain activation (Di et al., 2014). Whether an acute session of video gaming also transfers to better performance at Stroop task, or not, remains unknown.

## Purpose

This intervention is intended to test the alteration of the performance at a cognitive task for executive function (Stroop task) as well as related brain activity using fMRI to an acute bout of high-intensity physical exercise followed by a short session with a brain training video game in physically active and cognitively healthy older adults. It will be tested using a crossover design, so every participant acts as their own reference.

Some experiments have been conducted to investigate the long-term effects of physical exercise and video gaming on brain activity, but related to the acute effects, especially for the combination, the available literature is scarce. For physical exercise, some reports describe acute effects. Studies assessing video gaming as an acute intervention have been conducted, but no report has described an investigation of the acute effects of one session of video gaming on cognitive function, using either behavioral data or fMRI data. This report is the first of a study providing insight into how the brain activity and also the performance at the Stroop task might change in older people after an acute session of a combination of physical exercise and video gaming. With the design of this study, it is expected to be possible to compare between the physical exercise and video gaming conditions and to distinguish between their contributions on the improvement of cognitive function. Results from this study might not be suitable for the direct usage in daily life, but they pave the way for future studies investigating the combination of physical exercise and video gaming and their implications in daily life or in a clinical setting.

## Hypothesis

### Primary Hypotheses

Acute intervention with high-intensity physical exercise leads to significantly shorter reaction time at the Stroop task compared to intervention with low-intensity physical exercise.Acute intervention with the brain training video game Brain Age leads to significantly shorter reaction time at the Stroop task compared to intervention with the Tetris video game.Because an acute intervention of physical exercise might have a stronger effect on cognitive function than video gaming (McMorris and Hale, 2012; Bherer, 2015), the order for the other interventions with regard to the reaction time at the Stroop task is from short to long reaction time: (1) High intensity + Brain Age; (2) High intensity + Tetris; (3) Low intensity + Brain Age; and (4) Low intensity + Tetris.Acute intervention with high-intensity physical engenders stronger activations in DLPFC, VLPFC, and FPA compared to low-intensity physical exercise.Activation of R-FPA correlates with the performance (inversely with reaction time) at the Stroop task.Acute intervention with Brain Age video game leads to significantly different activation patterns from those obtained from intervention with Tetris video game, which also correlates with better performance at the Stroop task.

### Secondary Hypotheses

Expectations for improvement in various fields might differ in some regards (e.g., performance at cognitive task, performance at everyday tasks) between the experimental and the control task (high vs. low intensity or Brain Age vs. Tetris, respectively).Expectations of participants for improvement at the cognitive task (for both, physical exercise and video game interventions) correlate with the Stroop task performance (inversely with reaction time).Engagements of participants during experimental and control conditions (high vs. low intensity or Brain Age vs. Tetris, respectively) are not significantly different from each other.

## Methods

### Trial Design, Setting and Registration

This study is a randomized crossover controlled trial to test the response of Stroop task performance (cognitive task for executive function) and the related brain activity using fMRI to an acute bout of high-intensity physical exercise followed by a short session with a brain training video game in physically active and cognitively healthy older adults (60–70 years). In four sequentially applied interventions, the participants will undergo every one of the four combinations of experimental and control conditions (Figure 1). Participants are blind to the study’s hypothesis. The Consolidated Standards of Reporting Trials (CONSORT) statement (Moher et al., 2010) as well as the Standard Protocol Items: recommendations for Interventional Trials (SPIRIT) statement (Chan et al., 2013) were used as a framework for developing the study methodology (see Supplementary Tables S1–S3). For CONSORT, the extension for within-subject design (Pandis et al., 2017) as well as the extension for non-pharmacological trials (Boutron et al., 2017) have been considered.

**Figure 1 F1:**
[figure not shown]
Consolidated standards of reporting trials (CONSORT) flowchart.

The study will be conducted at the Smart Ageing Research Center, Sendai City, Miyagi Prefecture, Japan. Each participant in this study will provide written informed consent before participating. The protocol of the study and the consent form were approved by the Ethics Committee of the Tohoku University Graduate School of Medicine. This study is registered with the University Hospital Medical Information Network (UMIN) Clinical Trial Registry (UMIN000033054).

### Participants

Participants will be recruited from the general population through an advertisement in the local newspaper. Interested participants will be invited to visit Tohoku University for a more detailed screening assessment.

### Eligibility Criteria

The numbers of female and male participants are expected to be the same. All included participants are expected to be 60–70 years old and reported as right-handed, native Japanese speakers, with normal or corrected-to-normal vision, normal color vision, not concerned about their own memory functions, not using medications known to interfere with cognitive function (including benzodiazepines, antidepressants, and other central nervous agents), not to have any magnetic resonance imaging (MRI) contraindication (e.g., metal implants, being pregnant), and having no disease known to affect the central nervous system, including thyroid disease, multiple sclerosis, Parkinson’s disease, stroke, severe hypertension or diabetes. To have the same baseline, all participants were unfamiliar with video gaming; all report playing less than 1 h of video games a week during the prior 2 years (Basak et al., 2008). To minimize the influence of subclinical degenerative conditions and because this study is intended to assess the effects of an acute bout of high-intensity exercise on cognitively active older adults, the following exclusion criteria are applied. First, to screen for cognitive impairment, the Mini Mental Status Exam (MMSE; Folstein et al., 1975) and the Frontal Assessment Battery at bedside (FAB; Dubois et al., 2000) are applied. The MMSE is a widely used screening tool for detection of cognitive impairments in older adults. It consists of 20 items. They measure the orientation for time and place, memory and attention, and language skills and visuospatial abilities. The score range goes from 0 to 30, with lower scores indicating a greater degree of general cognitive dysfunction. Those participants with a score of 26 (Nouchi et al., 2012) or lower at MMSE are excluded. The FAB evaluates the executive functions and consists of six subtests for similarities (conceptualization), lexical fluency (mental flexibility), motor series (programming), conflicting instructions (sensitivity to interference), go–no go (inhibitory control), and prehension behavior (environmental autonomy). The score range goes from 0 to 18, with lower scores indicating a greater degree of executive dysfunction. Those participants with a score of 12 or lower at FAB are excluded. Second, those who are not sufficiently physically active and who might have an increased health risk while performing a vigorous exercise are screened. For that reason, the International Physical Activity Questionnaire (IPAQ; Craig et al., 2003) and the new Physical Activity Readiness Questionnaire (PAR-Q+; Bredin et al., 2013) are applied. Among IPAQ of different types, for this study, the Short Form 7 Days Telephone (IPAQ-S7T) will be used. This script is a cost-effective tool to assess physical activity: the interviewer must read out loud and it consists of seven questions related to the time the participant spends on different activities during the last week. Based on the answers, the participants can be assigned to three physical categories: LOW, MODERATE, or HIGH. Although some studies question the validity of the questionnaire (Lee et al., 2011), it provides insights into the physical status of the participant. Participants that have a category of LOW at IPAQ are excluded. The PAR-Q+, a pre-participation screening tool for people who wish to participate in physical activity (Goodman et al., 2011), gives a rough evaluation of whether there are risks that must be assessed before starting the physical exercise. It is a four-page document that can be completed in approximately 5 min. The first page has seven questions related to the health and medical conditions of the participant which can be answered with YES or NO. If responses to one or more questions are YES, then the next pages present follow-up questions that more narrowly specify the health concern. Participants answering one of the first seven questions with YES at PAR-Q+ are excluded. Furthermore, participants with a resting blood pressure over 140/90 mm (Piepoli et al., 2016) and those who do not feel comfortable with exercising during the familiarization phase are excluded. To avoid including possibly cognitive impaired participants, those with a Stroop task correct answer rate of less than 80% in the analysis are excluded.

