## Outcome

The primary outcome measures for all participants are the reaction time and correct answer count from the Stroop task as well as its related brain activity using fMRI after each of the four interventions. Additionally, the secondary outcome measures will be recorded similarly to the scores from the questionnaires for engagement after each intervention, the expectation after the familiarization phase and after the intervention phase, age, and gender at the first meeting.

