### Allocation and Implementation

Allocation of the participants to one of four sequences is done at the end of the familiarization phase (1 week before intervention phase) through a computer-generated sequence using random allocation software Graph Pad’s QuickCalcs Random Mumbers^1^. Based on a randomly assigned number list, the participants are allocated to each sequence.

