### Data Management

Personal information and data for all experiments are handled by the personal information manager director of Tohoku University. Access to information requires a key that is securely kept and has limited access. These internal checks and balances ensure the security of all data and personal information. After the experimental period ends, the data will be consolidated. Any information linking data back to the participant will be discarded to ensure that the data are truly anonymous. Data destruction will not be conducted.

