### Research Ethics Approval and Informed Consent

The Ethics Committee of Tohoku University Graduate School of Medicine approved the study protocol. They will approve the consent form. Participants will be given both an oral explanation and a written file that documents details of the study. Upon understanding, the participant will be asked to give written consent by signing the consent form. Participants might choose to withdraw from the study at any point in time. Should they choose to do so, their data would be destroyed.

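### The 80% Stroop accuracy cut selects the analysis set on a primary outcome measured after randomisation, and does not say which session or sessions it applies to

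*Protocol article*

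**What the plan says.** All references are to the protocol article.

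- **Eligibility Criteria.** After the cognitive, activity and blood-pressure exclusions, the section ends with the rule that "those with a Stroop task correct answer rate of less than 80% in the analysis are excluded". The stated reason is "To avoid including possibly cognitive impaired participants". MMSE and FAB cut-offs in the same section already screen for impairment.
- **Outcome.** "The primary outcome measures for all participants are the reaction time and correct answer count from the Stroop task", together with "related brain activity using fMRI after each of the four interventions".
- **Allocation and Implementation.** "Allocation of the participants to one of four sequences is done at the end of the familiarization phase", one week before the intervention phase.
- **Stroop Task Analysis.** The correct answer count is analysed with a generalised linear mixed model. The link function is not stated.
- **Discussion, Physical Exercise.** Accuracy on executive tasks after acute exercise is said to show no significant change or a small drop.
- **Sample Size.** The target is 24, taken from precedent. There is no power calculation and no stated allowance for losses.
- **Research Ethics Approval and Informed Consent.** "Participants might choose to withdraw from the study at any point in time", and then: "Should they choose to do so, their data would be destroyed".
- **Data Management.** "Data destruction will not be conducted", said of the data once the experimental period is over.

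**The concern.** Set side by side, these sections make a primary outcome the criterion for being analysed. A participant whose accuracy drops far enough after an intervention is removed, and with the accuracy data go that person's reaction times and images. If an intervention lowers accuracy, the rule tends to remove the people in whom it does so most, and the estimated accuracy effect moves toward zero.

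The rule is also not operational. It does not say whether the rate is taken in one session, in any of the four, or over all four together, nor whether congruent and incongruent trials are combined. Those choices give very different analysis sets and could be made after the data are seen.

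The withdrawal provision is a separate, smaller matter. A mixed model can use a participant with two or three completed sessions. If those sessions are destroyed, they cannot contribute, and nobody can check whether dropout was selective.

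**Working it through.** **The plan's own figures.** The target of 24 has no effect size, SD or power behind it, so there is nothing to reproduce. The trial count in Cognitive Task does check: 192×2 s of stimulus plus 96×2 s, 72×4 s and 24×6 s of interval gives 384 + 192 + 288 + 144 = 1,008 s = 16.8 min, as stated. So 192 trials per session is a sound input.

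**Step 1: what the undefined rule does to one participant.** Assume constant true accuracy *p* and independent trials.

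- One session: 0.8×192 = 153.6, so exclusion means 153 or fewer correct. q = P(Bin(192, p) ≤ 153).
- Any of four sessions: 1 − (1 − q)⁴.
- Pooled: 0.8×768 = 614.4, so P(Bin(768, p) ≤ 614).

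| True accuracy | One session | Any of four | Pooled |
|---|---|---|---|
| 82% | 23% | 64% | 8% |
| 84% | 7% | 24% | 0.2% |
| 90% | about 0 | about 0 | about 0 |

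At 82%: q = 0.227, and 1 − 0.773⁴ = 0.64.

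**Step 2: bias in the accuracy contrast (high minus low intensity).** From the documents: 24 participants, 4 sessions, 192 trials, 80% cut. Everything else is assumed, on the logit scale: mean intensity effect −0.3, between-person SD 0.6, SD of the individual intensity effect 0.5, session SD 0.3. Two codings were simulated: *centred* (the effect and its variation split equally between high and low sessions) and *high-only* (both fall on the high-intensity sessions). Whole participants are dropped. Entries are percentage points, with shrinkage = 1 − restricted/all.

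| Coding, median accuracy | All randomised | Pooled rule | Any-session rule |
|---|---|---|---|
| Centred, 90% | −2.95 | −2.56 (13%) | −1.71 (42%) |
| Centred, 95% | −1.67 | −1.63 (2%) | −1.40 (16%) |
| High-only, 90% | −4.2 | −2.6 (38%) | −1.2 (71%) |
| High-only, 95% | −2.6 | −2.3 (12%) | −1.5 (42%) |

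At 97% the pooled rule changes almost nothing under either coding. With a smaller effect SD (0.3) and session SD (0.25), high-only coding at 90% gives −3.63 to −2.77 for the pooled rule (24%) and −3.54 to −1.78 for the any-session rule (50%).

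**Step 3: the same contrast on the logit scale**, using empirical logits as a proxy for the mixed model. Centred coding, 90%: −0.300 for all, −0.294 pooled (2%), −0.247 any-session (18%). High-only coding, 90%: shrinkage of about 24% and 57%. Part of the loss in points arises only because removing low scorers moves the sample to a region where the same logit effect is worth fewer points.

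**Step 4: no average effect.** Under centred coding the rule then adds no bias. Under high-only coding the contrast shifts by up to about 0.6 points with effect SD 0.3 (median 87%, any-session: −0.34 to +0.28), and by about 1.3 points with effect SD 0.5 (median 90%, any-session: −0.85 to +0.41).

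**Step 5: numbers lost.** At 90% the pooled rule removes 2 to 3 of 24 (centred) or about 4 (high-only); the any-session rule removes about 7 or 9 to 10. The paired standardised effect detectable with 80% power at two-sided 5% (noncentral *t*, n − 1 df, noncentrality d√n) is 0.60 at n = 24, 0.63 at 22, 0.66 at 20 and 0.70 at 18.

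**The case against.** **It is an eligibility criterion.** The sentence sits under that heading, follows exclusions made during familiarisation, and aims at not including impaired people. Stroop is practised before allocation, so a pre-allocation screen may have been meant. That would be harmless. But the rule refers to the analysis, and no section describes a Stroop cut-off applied to practice data. If a screen was meant, the wording still has to change.

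**The size is uncertain.** This stands. The documents give no accuracy level, SD or effect. The sample is cognitively screened and well practised, so high accuracy is plausible, and there the pooled rule does little. A reader might take the 42% in the table as the expected bias. It is one assumed scenario in raw points; on the logit scale, the usual one for such counts, the same scenario gives 18%.

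**Reaction time is protected.** Largely right. The behavioural primary hypotheses concern reaction time. Dropping a whole participant removes all four conditions, so the within-person comparison survives, and an accuracy floor has some rationale for valid reaction times. A reader might infer that the reaction-time effect is biased. No calculation shows that; what remains is a selected sample, possible imbalance between sequences and fewer participants.

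**Withdrawal.** A reader might see a contradiction between Data Management and the consent section. The first concerns data after the experimental period and the second people who withdraw, so both can hold; only the wording needs clarifying. Nor do the documents show that withdrawal would follow high-intensity exercise (people uncomfortable with exercise are excluded during familiarisation) or that safety records would be destroyed.

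**Conclusion.** The point holds. As worded, the plan excludes randomised participants on a primary outcome measured after allocation, by a rule that can be read in at least three ways. At 82% true accuracy those readings give exclusion chances of 23%, 64% and 8%.

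If accuracy truly falls after an intervention, the estimated fall is biased toward zero. With an assumed logit effect of −0.3, the bias runs from negligible (pooled rule, accuracy 95 to 97%; 2% at 95% with centred coding, though 12% in points with high-only coding) to half or more (any-session rule, 90% accuracy, effect and its variation on high-intensity sessions only: 50 to 71% in points, about 57% in logits). For reaction time the supported harm is selection and lost numbers from a target of 24 with no stated allowance, not a demonstrated bias.

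The loss of withdrawers' completed sessions is real but secondary, and its effect cannot be sized from the documents.

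**What to change.** 1. Apply the 80% criterion to Stroop practice data from familiarisation, before allocation. State which practice session or sessions count and whether trial types are combined.
2. Keep every randomised participant and every completed session in the primary analysis of reaction time, accuracy and brain activity.
3. Run the 80% exclusion on post-intervention data only as a labelled sensitivity analysis, with the rule (one session, any session or pooled) fixed in advance and the number excluded reported by sequence.
4. Subject to ethics approval and consent, keep data collected up to withdrawal unless the participant asks for deletion. Analyse them in the mixed model, and report numbers and reasons by sequence and last condition. Reword the consent and Data Management sections so that each states which data and which period it covers.

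Cost: items 1 to 3 are wording, plus recording accuracy during practice that is already scheduled; a few noisy low-accuracy sessions stay in the primary analysis. Item 4 changes a commitment made to participants, so it needs ethics review and a revised consent form.
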